## Intervention delivery

The network strategy we outline is neither feasibly or sensibly delivered as a ‘big bang’ intervention. The relationships and processes on which it is based will take time to establish and mature. These temporal considerations lead us to propose that the intervention, in the form of network activities, is structured in phases that are outlined in
Figure 5. Phase 1 is dominated by developing the initial linkages across stakeholders and with NBU leaders building a shared vision and set of ambitions so that key personnel feel a sense of ownership of the change efforts. A key part of this phase is work to co-design tools and intervention components so that they facilitate or streamline work processes and help develop the team-based, trusting relationships that will be needed while simultaneously helping to embed shared aspirations for better care across all frontline workers. Four specific areas will be developed in this early phase that will be strengthened and sustained through subsequent phases. These include: i) work with hospitals to improve the quality of routine clinical information and the feedback mechanisms to be used to support improvement efforts at the national, senior hospital management and NBU team leader levels; ii) co-design of improved nursing charts to address the major problem of poor monitoring
^101^; iii) co-design of improved case review (audit) tools and processes that enable teams to engage positively and identify modifiable factors they can address to improve care locally; and iv) development of a communications skills training approach aimed at improving trust within teams and relationships between staff and families.

**Figure 5. f5:**
[figure not shown]
A simple representation of the activities planned as part of the network intervention outlining how we consider different phases within the overall approach. Intervention Phase 1 specific elements:
**1a –** Co-design, piloting and revision of job aides and newborn unit (NBU) mortality audit tools.
**1b –** Development and piloting of a short communications skills training for hospitals’ nursing leaders.
Intervention Phase 2 specific elements:
**2a –** Improve adoption of and adherence to Ministry of Health guidelines for inpatient neonatal care supported by use of finalised job aides and audit tools and provide regular feedback on performance at all levels of the health system.
**2b –** Improve team-working and communications through training, peer support and network participation for hospitals’ NBU team leaders.
Intervention Phase 3 specific elements:
**3 –** Continuous network participation at all levels of the health system with a focus to improve attention to addressing challenges that worsen neonatal survival and adequate post-natal weight gain in vulnerable babies.

Subsequent phases build from these foundations to strengthen communication and relationships across the network, including use of mentorship and peer to peer discussions to further develop the skills and shared purpose of those at all levels and address practical issues of improving day-to-day clinical NBU care. Feedback that recognises and celebrates positive change and sharing stories of such change across the network through online and face-to-face exchanges will, it is hoped, provide momentum and encouragement to those acting as champions at levels 1, 2 and 3 who we think of more formally as institutional entrepreneurs doing identity work.

## Evaluation study design

We have outlined our efforts to develop a large-scale change intervention strategy targeting NBU in multiple Kenyan hospitals that is based on our understanding of context, prior research and what to us are relevant theories. As researchers tackle improvement challenges at increasing scale, moving beyond specific clinical guidelines or care pathways, greater attention is being paid to ‘systems thinking’ and ‘complexity theory’
^59,
102^. These perspectives accept that interventions and contexts interact dynamically in ways that are not entirely predictable and seem particularly appropriate when changes in the behaviour of actors at multiple levels of the health system are needed. This does, however, mean that in designing an intervention strategy we must allow the process of intervention to remain somewhat flexible as ‘complex adaptive systems such as health care organizations and communities cannot be specified and managed in detail’
^103^.

In such circumstances the investigational approach may also need to remain flexible, within certain bounds. In experimental approaches the aim is tight control or standardisation of the intervention to preserve internal validity. Where this is not possible some have suggested experimental designs can incorporate flexibility in delivering components of the intervention provided that there is sufficient standardisation of the anticipated processes through which they are expected to work
^104,
105^. When it may be hard to standardise intervention strategies, either because they are not fully elucidated or because they are potentially numerous and interacting, then our evaluation design may have to be optimised to advance simultaneously our understanding of mechanisms, assess important outcomes and examine the links between the two. Our aim in intervention and evaluation design is therefore to focus on maximizing learning and research rigour.

Employing a clinical network as an intervention poses a number of specific evaluation challenges. The use of an experimental design that relies on use of randomisation and controls is problematic for a number of reasons. Here we briefly highlight some key issues. First, the unit of intervention is the network itself even if it comprises multiple organisations or facilities. In this sense the direct comparator should be absence of a network, reducing comparison to one intervention and one control observation which would represent a weak experimental design even if such a study was feasible. Some might consider facilities to be the unit of intervention, these then might be randomly allocated to participation in a network or as ‘controls’. We have previously discussed how randomisation may not achieve equivalence or balance in such a situation if only relatively small numbers of complex organisations such as hospitals can be included for reasons of feasibility
^106^. Amongst these is that the list of known and unknown factors (confounders) that may influence a hospital’s response to intervention is potentially very long and time-varying
^106^. For example, in Kenya these may extend from change in political or hospital leadership to localised strikes to distinct differences in disease epidemiology
^107,
108^. More specific to the LMIC context may be lack of data from control settings needed to evaluate intervention effects on quality or outcomes of care
^109,
110^. To gain such data researchers may have to create and embed new data systems which themselves become a form of intervention
^111^. Denying ‘control’ hospitals access to information that may help them improve poses clear ethical challenges. For multiple reasons, therefore, examining the effects of networks might best be conducted using longitudinal study designs without controls based on a programme theory while using both quantitative and qualitative strategies to examine effects linked to a plausibility framework
^112^. These evaluation designs may take the form of ‘in-depth, mixed-method case studies that pay attention to interconnectedness and incorporate an understanding of how systems come together as a whole from different perspectives’
^59^ and it is this form of evaluation we propose would be most useful to determine the effects of our network intervention and how it might produce both intended and unexpected effects.

### Our primary research question

How can a complex intervention comprising the development and sustained implementation of a multi-professional network (the change strategy) improve the quality of neonatal care and overall risk adjusted mortality in Kenyan hospitals and what transferable lessons can be identified that help advance programme theory to support future large-scale change interventions?

In tackling this overarching question, we will address a set of questions within sub-studies that advance our understanding of specific change efforts and effects.

1. Does co-design of job aides, audit tools and communications skills training improve their adoption and the quality of medical and nursing care?2. Which common factors need to be modified to improve inpatient neonatal care and outcomes?3. How do important process of care quality indicators change in response to feedback and how do these indicators and mortality change over the period of network participation?4. What is the optimum approach for risk adjustment so that variations in case-mix and case-severity can be accounted for when evaluating temporal trends in inpatient neonatal mortality?5. How do senior doctors and nurses’ social ties evolve within the network, influenced by face to face and online interaction, and influence the performance of frontline staff?6. How does information being produced by the network reach policy makers and other influential stakeholders and how might performance data be influential in fostering network growth and wider health system improvement?7. How can better performance measurement be integrated into national information systems to sustain improvement and future national networks?

In Phase 1 and extending into Phase 2 we will examine Questions 1 and 2. We will use data from a pre-intervention period and Phase 1 to develop and then deliver performance feedback on agreed quality indicators in Phase 2 and validate prognostic models for mortality (addressing Question 4) that can be used in future risk adjusted analyses of programme effects on neonatal outcomes. Across the phases of the intervention we will roll out the job aides, audit tools and communications training and link this with facilitative supervision, mentorship and peer learning with the aim of improving day-to-day clinical NBU care. Our aim is to intensify the focus on mortality reduction in Phase 3 using continued feedback and sharing stories of effective change across the MPN and with senior national level stakeholders. This will provide momentum and encouragement to key individuals at all organisational levels to strengthen change efforts. Data will be collected as the intervention matures through Phases 1, 2 and 3 to examine the evolution of the MPN and its effects (tackling specific Questions 3, 5 and 6) and explore how performance measurement might be integrated into the national health information system (addressing specific Question 7). Data on changes in quality indicators and mortality from across the pre-intervention period and Phases 1 to 3 together with qualitative data from across sub-studies will be employed in the Realistic Evaluation. Further information on the proposed conduct of sub-studies is provided in
Table 2.

**Table 2. T2:** Specific questions - sub-study designs and methods.

Study design and methodology	Study site; study populations; sampling procedures; and data collection procedures
***1. Does co-design of job aides and communications skills training support improve adoption of innovations and the quality of*** ***medical and nursing care***	
Rapid cycle co-design meetings with hospital staff of job aides (e.g. to support better documentation of vital signs observations and feed prescribing), structured team based case review (TCR audit) tools and to adapt an existing communications training will be used with pilot testing in these sites for an initial six months. ***(Completed)*** ***Currently -*** Introduction of new job aides and TCR audit tools is being progressively extended to MPN hospitals in the closing part of Phase 1 in preparation for Phase 2 when feedback on key indicators and MPN peer engagement will be used to promote their use. The adoption of job aides and their early effects on process measures of quality of care will be evaluated in Phase 2 to inform continued efforts to promote adoption.	*Study sites:* We will seek 2 - 3 MPN hospitals as volunteers for the rapid-cycle co-design activities prior to progressive pilot implementation in the remaining 8 - 9 hospitals. *Study populations:* Nurses and medical staff will be identified by hospitals to work with researchers to co-design job-aides and mortality audit tools and subsequently implement these. For piloting adoption of job aides, medical records of NBU admissions in the pilot period will be sampled. *Procedures:* Hospital records for NBU admissions for whom a co-designed job aide should be used / completed will be used to ascertain adoption and use these pilot studies data on up to 30 cases in 2-3 hospitals, allowing further redesign of job aides as needed. Notes and results of group meetings to co-design TCR audit tools and communications training will be used to assess the design process and improve tools prior to wider scale implementation as part of a Human Centred Design approach.
***2. Description of common modifiable factors in providing effective feeding to sick babies.***	
We will promote use of the structured neonatal TCR audit approach co-designed in Phase 1 across the MPN during Phase 2 and 3 to review late deaths occurring on the NBU (those ≥ 3 days post-natal age) to identify modifiable factors occurring during the NBU stay. TCR audit reports will be collated as part of MPN activities and aggregate reports generated on modifiable factors from across the 11 hospitals. Pooled data will be used to describe the nature and frequency of modifiable factors across hospitals.	*Study sites:* This work will include all 11 MPN hospitals. *Study* *populations:* Hospitals will be asked to review late post-natal deaths (those ≥ 3 days post-natal age at time of death) each month (noting that the Ministry of Health expects all neonatal deaths to be reviewed). *Data collection procedure:* Deidentified data will be collected from hospitals’ structured neonatal TCR audit reports. We aim to collect data on 250 cases as the basis for a report summarizing findings from all hospitals.
***3. How do important process of care quality indicators and mortality change over the period of MPN participation***	
Building on Phase 1 and the earlier establishment of the information system we will track and develop feedback systems on quality of practices such as feed prescribing, monitoring (e.g. assessment with pulse oximetry) and mortality outcomes and progressively use this to focus hospital teams’ attention on their performance in providing quality care and achieving good survival outcomes. We will aim to further drive local learning on how to improve care through online and MPN meetings between hospitals and promote the use of the information from locally conducted neonatal TCR audits that identify factors that can be modified to improve outcomes.	*Study sites:* This work will include all 11 MPN hospitals. *Study* *populations & sampling:* We will examine medical records for all NBU admissions in Phases 1, 2 and 3 and especially those meeting criteria of being a vulnerable baby (either preterm birth (<37 weeks gestation) or low birth weight (<2500g). *Data collection procedure:* All NBU records from which routine de-identified data are **currently being captured** and we will use the quality indicators developed (e.g. on feeding practices and correct antibiotic use) to provide monthly mortality reports and three monthly summary reports on quality of care indicators. We will track the change in aggregate and hospital specific performance and mortality outcomes over time.
***4. What is the optimum approach for risk adjustment of neonatal mortality so that variations in case-mix and case-severity can*** ***be accounted for when evaluating temporal trends in inpatient neonatal mortality***	
We will build on prior work undertaken in a single Kenyan hospital to develop two candidate prognostic scores for neonatal mortality and **use data already captured** to undertake external validation and improvement of these modelling approaches. The aim will be to develop a prognostic scoring approach that can be applied at individual patient level that enables us to undertake risk adjustment when tracking the long-term trends in survival outcomes in response to the MPN intervention.	*Study sites:* This work will include all 11 MPN hospitals. *Study* *populations & sampling:* We will use **existing data on over 30,000** **NBU** to validate / revise a preferred prognostic model and then use this model to provide risk-adjusted estimates of mortality each month for the 11 sites for a total of 36 months across Phases 1, 2 and 3. These data will enable us to say with greater certainty whether NBU mortality rates are declining over the period of intervention and potentially in which sub-populations.
***5. How do senior doctors and nurses’ social ties influence the performance of frontline staff and evolve within the MPN influenced*** ***by face to face and online interaction***	
Building on work to develop and implement the communications training we will progress to examine the relationships between medical and nursing staff within and between hospitals. This work will be informed by conduct of a realist review of social MPN analyses conducted on hospital staff and based on this proceed to empiric work involving in-depth interviews (IDIs) with senior hospital staff, small group discussions with frontline workers and family members, and episodes of non-participant observation of everyday practices. The aims of this data collection will be to explore changes in how MPN participants perceive their roles, their teamwork, the practices they employ to improve neonatal and family centred care and how these may all be mediated by the creation or strengthening of social ties resulting from MPN participation.	*Study sites:* Medical and nursing leads from all 11 MPN hospitals’ NBUs will be eligible for IDI and four hospitals representing maximum variation in performance on quality indicators being tracked will be identified for further IDI and small group discussions. In these four purposefully selected hospitals, non- participant observation will be conducted and front-line staff and family members will be invited for small group discussions based on convenience sampling but employing *inclusion criteria* to ensure diversity in respondents (e.g. based on age, qualification (for staff), gender and education (for family members) The aim is to conduct two small group discussions with staff (total four to six people) and families per site.
***6. How does information being produced by the MPN reach senior advisory and advocacy group members and how may it be*** ***influential in fostering MPN growth and wider health system improvement***	
The MoH Technical Group of Experts is expected to meet three times monthly in Phases 2 and 3. In the last 3 months of Phase 3 IDI will be conducted with group members and key wider stakeholders. We will explore their opinions on the value of the information being created by the MPN, their experience of their work as a group, and how such information might be used in the wider health system context to promote improved NBU care. Activities or reports have been of value in helping support decision making.	This work will focus on the national level and at the level of county administrations where these have hospitals included in the MPN. *In* *Phase 3* IDI will be conducted with members of the MoH Technical Group of Experts (n = 6 - 8), health care policy makers, key donor partner personnel (e.g. UNICEF, WHO) and selected senior county and hospital managers (total n = 6 - 10). *Sampling procedures:* Sampling will be purposeful with a snowballing approach used to identify relevant interviewees in national or county government, hospital management or donor organisations.

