**Figure 3. f3:**
[figure not shown]
Anchors in our reflective and iterative process that guided design of the specific Kenyan newborn unit intervention strategy. In this depiction we illustrate the major thematic factors we continuously navigated between as we sought, through an iterative and reflective process involving the authors and multiple team members, to link our understanding of context to potentially feasible intervention strategies aligned with our understanding of theories that offer potential mechanisms through which change is achieved.

Our overall Programme Theory is presented in
Figure 4. It draws generally on the theory and contextual influences outlined above but we use the structure of ‘If, then, because’ statements to propose much more specific requirements that should be achieved, assumptions that can then be examined in subsequent research (
Table 1)
^97^. At its heart is a central Multi-Professional Network. Operationally we aim that this will comprise two to three respected paediatricians (part-time) and a respected senior nurse (full-time) supported by a small team that supports data capture, analysis and timely performance feedback against key measures of the process and outcomes of care for up to 20 hospitals. In each hospital data are captured by abstracting from paper medical records by a single clerical assistant, a process that has previously proven successful
^99^. Electronic records are not used at scale in the Kenyan public sector
^100^.

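### Process indicators, and risk-adjusted mortality to the extent that its score uses the same items, are read from records whose documentation the intervention sets out to improve, so better recording can pass for better care

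*Protocol article*

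**What the plan says.** **Source of the data.** The section on the initial programme theory states: "In each hospital data are captured by abstracting from paper medical records by a single clerical assistant". These records supply the patient-level data for the process indicators and for the mortality model.

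**What the intervention changes.** Under Intervention delivery, one of four areas begun in Phase 1 and continued afterwards is to "work with hospitals to improve the quality of routine clinical information and the feedback mechanisms to be used". Another is redesigned nursing charts, aimed at poor monitoring. Table 2, sub-study 1, describes job aides meant "to support better documentation of vital signs observations and feed prescribing", and says that they reach the wider network towards the end of Phase 1.

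**What is measured.** Table 2, sub-study 3, tracks "quality of practices such as feed prescribing, monitoring (e.g. assessment with pulse oximetry) and mortality outcomes".

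**How mortality is adjusted.** The text before Table 2 says of indicator development and model validation: "We will use data from a pre-intervention period and Phase 1". Sub-study 4 aims to "develop a prognostic scoring approach that can be applied at individual patient level that enables us to undertake risk adjustment", and will then "use this model to provide risk-adjusted estimates of mortality each month for the 11 sites for a total of 36 months", across Phases 1 to 3. The article expects this to give greater certainty about whether mortality is declining.

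**The concern.** The intervention and the measurement share one instrument, the paper record. A pulse-oximetry check that was made but not written down before the new chart counts as not done. Once the chart has a place for it, the same check counts as done, and the indicator rises with no change at the cot side.

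The adjusted mortality series could be affected in a similar way. The model learns the relation between recorded items and death mostly from records that precede network-wide use of the new job aides, and is then applied to later records. If some score items become better recorded, the expected number of deaths moves although the babies are no sicker or healthier.

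Recording would change in step with the intervention, so a longer series does not separate the two. The article acknowledges, under Evaluation study design, that a new data system can itself act as an intervention, but uses this only as an argument about control hospitals. At stake is how far a rise in an indicator, or a fall in adjusted mortality, can be attributed to the network.

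**Working it through.** **1. The plan's own precision.** Inputs from Quantitative analyses and sample size: 1200 babies and 400 low-birthweight babies a month, proportion 50%. Half-width = 1.96 × √(p(1−p)/n).
- n = 400: 1.96 × √(0.25/400) = 4.9 points (stated ±5).
- n = 1200: 1.96 × √(0.25/1200) = 2.8 points (stated ±3).

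Both figures reproduce and are not in dispute. They serve as a scale for what follows.

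**2. Process indicator.** Indicator = true delivery × proportion of delivered care that is recorded. The article gives no recording rates, so these are assumptions.
- Delivery fixed at 50%, recording 70% to 95%: 0.50 × 0.70 = 35%; 0.50 × 0.95 = 47.5%; shift 12.5 points.
- Delivery fixed at 70%, same recording: 49% to 66.5%; shift 17.5 points.

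Both shifts are well beyond 2.8 or 4.9 points.

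**3. Adjusted mortality, unrecorded read as normal.** Assumptions: true mortality constant at M = 10% (the article's baseline); one severity sign with prevalence q and risk ratio RR; recording c0 when the model is fitted and c1 later.
- Risk without the sign: r0 = M/(1 − q + q·RR). Risk with it: r1 = RR·r0.
- Fitted risk when no sign is recorded: neg = [(1 − q)r0 + q(1 − c0)r1] / [1 − q·c0].
- Later expected mortality: E = q·c1·r1 + (1 − q·c1)·neg.

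Example with q = 20%, RR = 3, c0 = 70%, c1 = 95%:
- r0 = 0.10/1.40 = 0.0714; r1 = 0.2143.
- neg = (0.0571 + 0.0129)/0.86 = 0.0814.
- E = 0.19 × 0.2143 + 0.81 × 0.0814 = 0.1066; O/E = 0.10/0.1066 = 0.94.

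Over q = 10–30% and RR = 3–5:

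| Recording, early to late | O/E at q 10%, RR 3 | O/E at q 30%, RR 5 |
|---|---|---|
| 80% to 95% | 0.98 | 0.93 |
| 70% to 95% | 0.96 | 0.89 |
| 50% to 90% | 0.94 | 0.85 |

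Adjusted mortality (10% × O/E) would then read 9.8% down to 8.5% with deaths unchanged.

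**4. The same change under other coding** (q = 20%, RR = 4, so r0 = 0.0625 and r1 = 0.25; recording about 50% rising to 90%).
- Separate category for missing: O/E = 1.00 if recording is unrelated to the sign; 0.99 if babies with the sign were recorded less often at first (40% v 55%); about 1.02 if more often (70% v 45%).
- Missing read as abnormal: the fitted abnormal group is 0.20 + 0.80 × 0.50 = 0.60 of babies, with risk (0.05 + 0.025)/0.60 = 0.125. Later it is 0.20 + 0.80 × 0.10 = 0.28. E = 0.28 × 0.125 + 0.72 × 0.0625 = 0.08; O/E = 1.25, an apparent worsening.

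The sign of the artefact therefore depends on the coding.

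**The case against.** **The mortality part rests on facts that the article does not give.** It names neither the score items nor the handling of missing values, and those details may properly sit in a fuller document. Nothing shows that the score uses the vital-sign or feeding items that the charts target. If it rests on items such as birth weight that are well recorded throughout, the artefact is small. This stands, and it limits the mortality part to a conditional statement. The absence of those details is not the complaint.

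**Crude mortality is also tracked.** Recording of predictors cannot alter deaths per admission. A reader might set the O/E figures against the article's example of a fall from 10% to 8% and infer that recording alone could produce it. The documents do not support that inference, because the example is explicitly crude mortality. A fall in adjusted but not crude mortality would be visible.

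**A feed prescription is a written order**, so care given but not written down fits it poorly. This stands too: the indicator problem is firmest for monitoring.

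**The design claims plausibility from several sources.** It adds national-system (DHIS2) data from at least 30 other hospitals and non-participant observation in four network hospitals. These help only in part. The article itself reports considerable weaknesses in the national data, describes no risk adjustment of them, and they cannot reveal recording drift inside network hospitals. The observation concerns roles, teamwork, practices and social ties, and is not described as a check on the indicators.

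**Conclusion.** The point holds for the process indicators, above all monitoring such as pulse oximetry. Documentation is both a target of the intervention and the means of measurement, and plausible recording gains shift an indicator by 12.5 to 17.5 points against a monthly precision of about 3 to 5. The recording rates are assumed; the coupling is documented.

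For risk-adjusted mortality the point is conditional. The series is exposed to the extent that the score uses items whose recording improves after the fitting period. With one sign of risk ratio 3–5 and unrecorded read as normal, O/E falls to between 0.98 and 0.85 with no change in deaths. Under other coding it stays near 1 or rises to 1.25. A reader might conclude that adjusted mortality will drift downwards, or that both quantitative outcomes could improve unnoticed with survival unchanged. The documents support neither, since the direction is undetermined and crude mortality offers a partial check.

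**What to change.** **Sub-study 4.** Run the risk-adjusted series a second time using only predictors whose recording is shown to be stable across phases (birth weight, sex and age at admission are candidates if completeness confirms it). Do not score unrecorded signs as normal. Present this series beside the full-score series, crude mortality and the monthly completeness of each score item. Where the full-score trend disagrees with the stable-item or crude trend, do not attribute a decline to the network until the difference is explained.

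**Sub-study 3.** Keep all eligible babies in the denominator. In addition, report the recorded component and the correct-among-recorded component where the second has a meaning, such as feed prescribing. The latter should not become the main measure: it drops babies with nothing recorded, and so would hide the missed care that the article's account of Kenyan newborn units describes as a main problem. Interpret a rise in a monitoring indicator that coincides with chart introduction as possibly a recording change.

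**Cost.** Extra wording and extra runs on data already abstracted. The stable-item model adjusts less for severity, so it accompanies the full score and neither replaces nor overrules it.
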